## Abstract

**Background:**

Sedentary behaviour (SB) and low levels of physical activity (PA) are predictors of morbidity and mortality. Tertiary employees spend a considerable amount of their daily time seated and new efficient strategies to both reduce sedentary time and increase physical activity are needed. In that context, the REMOVE study aims at evaluating the health effects of a 24-week cycling desk intervention among office workers.

**Methods:**

A prospective, open-label, multicentre, two-arm parallel, randomized controlled trial (RCT) will be conducted in office-sitting desk workers. Office workers (*N* = 80) who have 0.8 full time equivalent hours (FTE) and 75% of this time in a sitting position will be recruited from tertiary worksites in Clermont-Ferrand, France. Subjects will be randomly assigned to one of the two following interventions: (i) PPM6: performance of two 30 min of cycling desk (using portable pedal exercise machine—PPM) per working day for 6 months or (ii) CTL_PPM3: 3 months with no intervention (control) followed by 3 months during which workers will be asked to complete two 30 min of PPM per working day. At baseline (T0), at 3 months (T1) and at 6 months (T2) after the start of the interventions, primary outcomes; 7-day PA and SB (3D-accelerometers), secondary outcomes; body composition (bioelectrical impedance), physical fitness (aerobic fitness, upper and lower limb strength), metabolic outcomes (fasting blood samples), self-perceived stress, anxiety, quality of life at work and job strain (questionnaires), tertiary outcomes; resting metabolic rate and cycling energy expenditure (indirect calorimetry) and eating behaviours (questionnaires) will be measured. An ergonomic approach based on observations and individual interviews will be used to identify parameters that could determine adherence.

**Discussion:**

The REMOVE study will be the first RCT to assess the effects of cycling workstations on objectively measured PA and SB during working and non-working hours and on key physiological and psychological health outcomes. This study will provide important information regarding the implementation of such cycling workstations in office workers and on the associated potential health benefits.

**Trial registration:**

ClinicalTrials.govNCT04153214. Registered on November 2019, version 1

## Background

Sedentary behaviour (SB) is defined as any waking behaviour characterized by an energy expenditure ≤ 1.5 metabolic equivalents (METs), while in a sitting, reclining or lying posture [1, 2]. Time spent sedentary and low levels of physical activity (PA) are known to be major predictors of cardiometabolic risks [3, 4]. Epidemiological studies further suggest that people engaged in prolonged (uninterrupted) have higher cardio-metabolic risks than people who regularly break up their sitting time, independent of the total time spent sitting and physically active [5, 6].

SB has continuously increased over the last century due to environmental changes, including technology, structure of industries, automation and computerisation [7–9]. With the emergence and expansion of the tertiary activities, the occupation domain has largely contributed to the general adoption of SB, especially with the generalization of the desk-bound activities [10]. For instance, during an 8-h working day, office workers spend on average about 77% of the time sitting, 18% standing and only 5% in other activities [11]. Office workers are therefore particularly vulnerable to the adverse health effects of SB.

Thus, the workplace represents an ideal setting to implement strategies to promote PA and reduce SB, especially prolonged SB, and thus improve employee’s health [12, 13]. Recently, various strategies to reduce sedentary time in the workplace have been developed [14]. The use of active workstations such as desks coupled with a treadmill, a cycling station or step have been reported to reduce sedentary time at work and increase PA [15] along with positive health effects [16]. Most of these studies were conducted in individuals suffering from overweight or obesity and tested whether such workstations were efficient to increase daily energy expenditure. However, data in normal weight people to support the preventative effect of such strategies remain scarce [17]. In addition, the long-term effectiveness of programs using active workstations to increase PA and reduce SB on time spent sedentary (total duration, average duration of each bout, number of breaks, etc.) and physically active but also on key biological parameters have not been determined yet [18, 19]. Assessing the effect of such a strategy on physical fitness is particularly relevant given that both endurance capacity [20–22] and muscle strength [23] are powerful predictors of mortality and morbidity independent of the health status of the individuals.

Interventions should not only focus on the operational feasibility but also consider the potential side-effects on the employees’ work task quality and productivity. Interventions aiming at increasing PA and reducing SB in office workers should assess the coherence and compatibility with the working environment, structuration, culture and the way they live and experience their work [24].

To date, results on the effects of interventions in the work environment to reduce SB are not clear-cut, potentially because of the limited number of studies, the relatively low samples sizes, the heterogeneity in the study designs and the lack of highly rigorous studies. Based on this observation, Shrestha et al. concluded on the need for long-term, multi-place, randomized controlled studies with objective measurement of PA and SB not only during the work period but also outside of work [19]. On top of these methodological issues is the use of treadmills or cycling desks in most of the available studies; the implementation of these devices is however limited because of their high cost, large size (that may not fit in small offices) and lack of portability [25]. Portable pedal machine (PPM) have been recently designed and proposed for such interventions. They can be settled under a desk, sparing a lot of space, and are easy to use. They open new possibilities for the development of strategies aiming at fighting against SB in tertiary worksite [16, 25].

## Objectives

The primary objective of this study is to evaluate the effects of a cycling workstation program (30 min twice a day) for 3 months among tertiary employees on PA and SB during working and non-working days. Our secondary objective is to assess the effect of this cycling workstation program on body composition, physical fitness and cardiometabolic risk factors (composite measure of fasting glucose, insulin, triglycerides, HDL-cholesterol, LDL-cholesterol, C-reactive protein or CRP, blood pressure and heart rate variability) and psychological parameters. Our third objective is to do an ergonomic assessment and determine the effects of this cycling workstation program on resting metabolic rate, cycling energy expenditure, eating behaviour and the implementation of the device in the worksite. Finally, we will extend the initial 3-month intervention with 3 additional months and thus test the 6-month effects of the intervention on the above-mentioned outcomes.

## Hypothesis

We hypothesize that the daily use of a cycling workstation for 3 months will increase PA and reduce SB on both working and non-working days and will improve physical and psychological health outcomes compared to a control condition with no intervention. The addition of three extra months of intervention (i.e. 6 months total) will further improve the study parameters compared to the effects that will be observed after 3 months of intervention.

## Methods and analysis

### Study design

The REMOVE study is a prospective, exploratory, randomized, controlled, open-label, multicentre, two-arm parallel trial in office-sitting desk workers (Fig. 1).

**Fig. 1 Fig1:**
[figure not shown]
Study overview

Eighty tertiary employees from Clermont-Ferrand (France) will be recruited to participate in this protocol. Three worksites of moderate size (*n* = 80 employees across the 3 sites) will be randomly assigned to one of the two interventions: (1) CTL_PPM3, an intervention with two consecutive periods: 3 months with no change of working conditions (CTL: control phase) and 3 months of PPM use (PPM3), and (2) PPM6, an intervention with 6 months of PPM use. Tests will be performed on both groups at baseline (T0), after 3 (T1) and 6 months (T2) of the intervention. Information sheets will be given to all the participants and written informed consent will be obtained for each participant. This study has been approved by the ethical authorities (CPP IDF VIII 19 09 66) and registered as a clinical trial under the reference number NCT04153214 (clinicaltrials.gov).

### Study setting and eligibility

Worksites will be recruited in Clermont-Ferrand, Region Rhones-Alpes-Auvergne, France. Selected worksites will be drawn from distinct work sectors: administration of the Universities, healthcare administration and school board.

### Study eligibility

#### Worksite eligibility criteria

Worksites will be selected if they respond to the following criteria: desk-bound job employees, no use of sit-stand desk or other active working station, every CEO agrees that participants will do the three test sessions (2 h each) during working hours. The worksites will not interact between each other.

#### Participant eligibility criteria

Participation is voluntary. Participants will be recruited if they fulfil the following criteria: aged 18–61 years, BMI ≤ 29.9 kg/m^2^, are employed more than 80% full time with 75 % of this time in a sitting position (seated office work such as computer or telephone-based work), do not have a contact job where the PPM can be badly experienced by the visitor, do not practice PA more than 2.5 h per week, are able to cycle for 30-min per session and 60-min per day and agree to be randomized.

#### Participant exclusion criteria

Employees will not be included if they have acute or chronic infections, oncological diseases, joint replacements or any surgery within the previous 6 weeks, psychiatric disorders, are pregnant or breastfeeding women, have diabetes treated with insulin and any condition that might affect the use of the PPM.

### Protocol status

#### Recruitment of participants

At the selected sites, an informal session will be conducted among employees, detailing the objectives of the study and the protocol. Following this first meeting, volunteers will inform their managers and the investigators of their willingness to participate. Then, they will have a screening visit with a member of the study team to verify inclusion and exclusion criteria and sign a written informed consent. Prior to any inclusion, study requirements will be repeated and participants will be able to withdraw from the study at any time without giving any explanation.

#### Randomization

A permuted-block randomization (i.e. random block sizes) will be conducted by the study biostatistician using a computer-generated random allocation (Stata software, version 15, StataCorp, College Station, US), with a 1:1 ratio allocation, ensuring complete randomness of the assignment of a patient to each randomized group. The randomization will be stratified by centre. The randomization and allocation process will be performed by the statistician involved in this study. Physicians will be involved for the enrolment participants.

### Intervention

The objective of the study is to replace 30 min of sedentary time by 30 min of PA of light intensity (LPA), twice a day, during the five working days (i.e. 60 min/day). Therefore, office workers should accumulate 5 h of LPA per week. This study design choice was motivated by recent observations from epidemiological studies. The replacement of 60 min per day of sedentary time by LPA has been associated with a decrease in the risk of all-cause mortality by 40% in a study [26] and 18 % in another one [27].

Volunteers will be provided PPM (DeskCycle, 3D Innovations LLC., Greeley, CO, USA). The device requires only little space and can be slipped under the desk while using it or not.

Subjects enrolled in PPM6 group will be equipped with a PPM under their desk and will use it 60 min per working day (30 min continuously in the morning and 30 min in the afternoon) during 6 months.

Subjects in the CTL_PPM3 group will maintain their habitual daily activities during the first 3 months. Then, they will also have a PPM under their desk and will use it 60 min per working day (30 min in the morning and 30 min in the afternoon) during the next 3 months. The time of use in the morning or afternoon is left to the choice of the subjects and may change from one day to another.

Before using the PPM, every participant will have a familiarization visit for the use of the device. Thus, if needed, their workstation will be adapted to adjust their seat with the Deskcycle. While the PPM proposes 8 levels of magnetic resistance, all the participants will perform their cycling exercises at the same intensity (resistance level 2) that allows to pedal with a minimum of resistance. The speed will be chosen by participants to not disturb them during their work. PPM has a monitor to inform users about the completed total distance, duration of exercise, speed of cycling and revolutions per minute (RPM). Subjects will fill up a notebook on a Microsoft Excel files to inform investigators of what he/she did at each session of cycling (performed : yes or no, completed distance, time and duration of cycling) that will be gathered every week by the study team. This information will be used to estimate participants’ adherence to the intervention.

Notebooks will inform us if participants properly completed the intervention. Pop-up reminders will be sent via emails to the participants twice a day (1 h before lunch break and 1 h before the end of daywork) and will contain information regarding the overall effects of sedentary time on health and on the benefits of PA. Pop-up notifications will be used if participants will not reach three times in a working week the 30 min per half-day. Such motivational approach has been shown to be efficient and will be used here to motivate participants to maintain the requested 60 min of cycling per day [25]. Every week, a member of the research team will meet the participants at their workplace to have direct feedback on their use of the PPM and to keep their level of engagement as high as possible. Each participant should keep their daily activities and care without any modification except those asked in the protocol.

### Data collection

All measurements will be performed on three different occasions: baseline (T0), 3 months (T1) and 6 months (T2). Figure 1 and Table 1 present the overall study. All the clinical measurements will be done at the Laboratory of the Metabolic Adaptations to Exercise under Physiological and Pathological Conditions, in Clermont-Ferrand (France).

**Table 1 Tab1:** Measurements timeline for both groups

Measurements timeline for both groups			
Measurement	Baseline	3 months	6 months
Socio-demographic data	X		
Objectively measured of PA and SED	X	X	X
Self-reported lifestyle behaviours	X	X	X
Health-related outcomes	X	X	X
Body composition	X	X	X
Physical fitness	X	X	X
Metabolic outcomes	X	X	X
Stress and anxiety	X	X	X
Life span and quality	X	X	X
Resting metabolic rate	X	X	X
Satisfaction and adherence			X

### Socio-demographic data

At baseline, socio-demographic data including age, gender, education level, marital status, household composition, number of children living in the household and employment status (i.e. length of tenure, working hours, overtime hours and job classification) will be collected. Also, medications and/or altered doses of an existing treatment over the last 3 months will be recorded. At T1 and T2, participants will be asked to report any life events that may have occurred over the past 3 months that may have affected their health or wellbeing.

### Primary outcomes

#### Physical activity level and sedentary time

Two devices will be used, to ensure a more precise evaluation of PA [28]. Daily light, moderate, and vigorous PA will be measured objectively with the tri-axial Actigraph GT3x-BT monitor (AG) (Actigraph LLC, Pensacola, Fl, USA). This monitor will be worn at the waist above the right hip with an elastic belt during 5 days [29]. Participants will be asked to wear AG during all their waking hours, except during water-based activities. This device is accurate to classify PA in daily life environments [30] and have been validated in adult population [31].

The second device used is an activPAL3 micro (AP) (PAL Technologies Limited, Glasgow, UK; default settings) worn on the mid-line of the right thigh. This inclinometer monitor will be worn continuously during the same 5 days than the AG except during water-based activities. ActivPAL3 micro has been validated to evaluate time spent sitting/lying, standing, walking, number of sedentary bouts and number of breaks of those sedentary bouts [32, 33]. Participants will be asked to precisely indicate when they will use the PPM since AP might not be sensitive enough to detect this behaviour [34].

During each measurement period, subjects will report their exact bed time, wake up time, time they start wearing the activity monitors and time when they took them of. Participants will also be asked to report the time they arrive at work and leave from work as well as any period of not wearing the monitors. This information will be used to calculate the variables from the activity devices during the entire day on both working and non-working days. Time spent active and sedentary will also be assessed during the working hours and non-working hours of the working days.

### Secondary outcomes

#### Health-related outcomes

Blood pressure will be measured three times at each visit on the right arm of the participant who will be in a seated position. Only the last value will be reported.

For anthropometric measurements, participants will wear light indoor clothing without shoes. Body height will be assessed with a stadiometer. Value will be taken to the closest 0.1 cm. Body weight will be assessed to the closest 0.1 kg with a scale (Tanita MC-780, Tanita, USA, Arlington Heights). Thereby, body mass index will be calculated using following formula BMI = weight(kg)/ height(m)^2^.

Waist circumference (WC) will be measured with a tape measure to the nearest 0.5 cm, and WC to height ratio (WHtR) will be calculated. This ratio is a better predictor of intra-abdominal fat mass than WC alone [35] in both men and women [36].

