### Sample size and power calculation

Sample size estimation is based on CONSORT 2010 statement for the comparison between randomized groups. In these statements, Eldridge et al. suggested “that the size of a trial should be related to the size of the future definitive RCT and for such a trial designed with 90% power and two sided 5% significance” [109]. They “recommend trial sample sizes for each treatment arm of 75, 25, 15, and 10 for standardized effect sizes that are extra small (0.1), small (0.2), medium (0.5), or large (0.8), respectively”. Considering a two-sided type I error at 5% and a statistical power greater than 80%, an effect size of 1 can be assumed for the PA and SB levels score with 18 patients per group. To take into account the lost to follow-up, a maximum of 80 patients (20 by arm, 50% females) will be included in the study.

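### Reporting only the last of three blood pressure readings gives up a small amount of precision that averaging readings 2 and 3 would recover at almost no cost

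*Protocol article*

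**What the plan says.** Under Health-related outcomes, the protocol article specifies that "Blood pressure will be measured three times at each visit on the right arm of the participant", with the participant seated. The last sentence of that paragraph is "Only the last value will be reported". No reason is given, and no other section averages the readings or uses the first two.

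The visits are "baseline (T0), 3 months (T1) and 6 months (T2"). Blood pressure is a secondary outcome. It also appears in the Objectives as part of the composite of cardiometabolic risk factors, whose list ends with "C-reactive protein or CRP, blood pressure and heart rate variability".

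Statistical analyses handles continuous secondary endpoints in the same way as the primary one: first a Student's t or Mann-Whitney test, then a multivariable mixed model. Longitudinal random-effects models with a group-by-time interaction are planned as well. Secondary endpoints are described as exploratory.

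**The concern.** A single cuff reading contains error that differs from one reading to the next within the same visit. Averaging readings reduces that component, and here the extra readings are already scheduled. Using only the third leaves the whole component in the analysed value, both at follow-up and at baseline wherever baseline is used.

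What is at stake is the width of the confidence interval for blood pressure, and to a smaller degree for the composite, in a trial of at most 80 people. The size of the loss depends on the analysis. Where stable differences between people are removed by baseline adjustment, reading error is a larger share of what remains.

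**Working it through.** **The plan's own figure.** None is given for blood pressure. The only stated calculation is for the primary outcome: "an effect size of 1 can be assumed for the PA and SB levels score with 18 patients per group", with two-sided 5% error and power above 80%. That reproduces: an exact two-sample t test with 18 per group and a standardised effect of 1 has 83.0% power. Blood pressure does not enter it, so nothing below affects it.

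**Inputs.** From the protocol: three readings per visit, the last one used, visits T0, T1 and T2. Assumed, because the protocol gives no variances: reading SD s_r = 3–6 mmHg, visit-to-visit SD s_v = 4–5, between-person SD s_b = 9–12. These imply a correlation between readings at the same visit of about 0.73 to 0.95.

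**Formulas.** For the mean of k readings:

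- Total variance: T(k) = s_b² + s_v² + s_r²/k.
- Unadjusted comparison of follow-up values: the SE ratio against one reading is √(T(2)/T(1)); the equivalent gain in participants is T(1)/T(2) − 1.
- Baseline-adjusted comparison: the correlation between visits is s_b²/T(k), and the residual variance is A(k) = T(k) × [1 − (s_b²/T(k))²]. The SE ratio and the gain follow in the same way from A(2) and A(1).

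Only the term s_r²/k changes with k. With k = 2 its variance is halved (its SD falls by 29%). The visit-to-visit and between-person terms do not move.

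**Results for the mean of readings 2 and 3, at the extremes of the assumed ranges:**

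| Analysis | s_r, s_v, s_b | One reading | Mean of two | SE reduction | Equivalent extra participants |
|---|---|---|---|---|---|
| Unadjusted, smallest gain | 3, 5, 12 | T = 178.0 | T = 173.5 | 1.3% | 2.6% |
| Unadjusted, largest gain | 6, 4, 9 | T = 133.0 | T = 115.0 | 7.0% | 15.7% |
| Adjusted, smallest gain | 3, 5, 9 | A = 57.95 | A = 51.12 | 6.1% | 13.3% |
| Adjusted, largest gain | 6, 4, 12 | A = 90.20 | A = 61.51 | 17.4% | 46.7% |

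Example for the first row: T(1) = 144 + 25 + 9 = 178 and T(2) = 144 + 25 + 4.5 = 173.5, so the SE ratio is √(173.5/178) = 0.987.

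**Illustration on the power scale.** With 40 per arm, an unadjusted comparison and a true difference of 0.5 single-reading SD (an assumption), power by normal approximation is 60.9% with one reading. With the mean of two readings it is 67.9%, 65.4%, 63.1% and 62.0% at same-visit correlations of 0.7, 0.8, 0.9 and 0.95.

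**The case against.** The best defence is that keeping the last reading is a settling rule: the first readings let the participant adapt, and the third is the cleanest. The protocol does something similar for resting metabolic rate, where it reports only the final 5 minutes of a longer recording. If readings drift down within a visit, or early ones are more variable, the equal-variance assumption fails and averaging gains less. This part stands as a caution. However, the article does not give this reason for blood pressure, and a mean of readings 2 and 3 still drops the first reading.

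It is also fair to say that every variance is assumed, so only the direction is secure. The analysis listed first is the unadjusted test, where the gain is small. The baseline covariates named for the mixed model are those of physical activity and sedentary behaviour, so adjustment for baseline blood pressure depends on how the same approach is carried over to this endpoint. The composite has eight listed components, so any gain there is diluted; it has not been quantified.

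A reader might infer that the first two readings are thrown away. The text says which value is reported; it does not say that the others go unrecorded, and the case report form is not shown. A reader might also infer bias in the treatment comparison. The same rule applies to both arms at every visit, so the documents give no ground for that.

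**Conclusion.** The point holds as a minor efficiency loss. The rule is clear and can be carried out, but it is less precise than a mean of the last two readings if these have similar variance and a correlation below 1. Under the assumed SDs, that mean lowers the standard error by about 1–7% unadjusted and about 6–17% with baseline adjustment. The equivalent gains in participants are 3–16% and 13–47%.

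The larger range should not be read as the general cost, because it needs baseline adjustment for blood pressure. Nor does averaging halve the measurement error as a whole: it halves the variance of the reading-level component only. The effect is confined to an exploratory secondary outcome and one component of the composite, and the primary objective is untouched.

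**What to change.** In Health-related outcomes, replace the last-value sentence with: *The mean of the second and third readings will be analysed at T0, T1 and T2, and the same value will be used in the composite.*

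If all three readings are on the case report form, the cost is this one sentence plus entering two values instead of one, and it can be settled before analysis. Trial status reports that recruitment finished on 15 March 2021, so some visits may already be complete. If earlier readings were not recorded at such a visit, the sponsor should say so and use one consistent rule at all visits, so that baseline and follow-up values are not defined differently.
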